### Research design and sampling

This feasibility quasi-experimental study with a control group was reported in accordance with the Consolidation Standards of Reporting Trials (CONSORT) statement for pilot and feasibility trials (Additional file 1) [17]. The current study will be conducted on 165 primiparous women with 18-20 gestational weeks that will be selected by convenience sampling method. The researcher will attend the prenatal clinic for sampling on a daily basis. The participants will be equally allocated into two studies and one control groups (Fig. 1). The participants in study groups A and B will receive virtual and in-person childbirth preparation trainings, respectively. Also, the control group will receive no education on childbirth preparation during pregnancy.

**Fig. 1 Fig1:**
[figure not shown]
Key points for data collection

### Intervention

In the study group A, a Telegram room entitled: “Virtual childbirth preparation training courses” will be created for uploading the educational content. In addition, another Telegram room will be created with the same name in which, the participants could ask their questions and receive answers. The content of virtual education will be provided based on the standard regulations of Iran and also, the Mayer’s principles of multimedia learning [18] using text, picture, video clips, podcast, and MPEG4 (MP4) videos. Moreover, the maximum size of educational files will be 50 MB in the form of 5-15 min long videos.

To increase the quality of training and prevent sending the whole content at once, the content of each session will be provided in relevant files that will be uploaded at a specific time (except for Thursdays and Fridays). In total, the educational contents will include six PDF files; 21 videos; four podcasts about relaxation and breathing techniques during labor; 14 video clips; and 64 MP4 video files about exercises during and after pregnancy, massage, labor positions, birth ball exercises, and postpartum exercises. The contents will be uploaded directly on the Telegram rooms as shown in Table 1.

**Table 1 Tab1:** The educational content of virtual and in-person childbirth preparation training courses for the study groups A and B

Time	Content	Objectives	Uploading the virtual content to the Telegram room
First session: 20-23 gestational weeks	-Personal hygiene with an emphasis on anatomy and physiology during pregnancy	-An introduction to the reproductive system -Changes and adaptations of the body during pregnancy, common complaints and coping strategies -Personal hygiene	4 video clips for theoretical content 9 videos (1) for exercises during pregnancy 1 podcast for relaxation (1)
Second session: 24-27 gestational weeks	-Pregnancy diet	-Pregnancy diet with emphasis on what to eat -An introduction to the food pyramid	1 video clip for theoretical content 9 videos (2) for exercises during pregnancy Repeating relaxation (1)
Third session: 28-29 gestational weeks	-Mental health during pregnancy	-An introduction to the fetal growth and development -Preparing for motherhood -Preparing for fatherhood	2 video clips and 1 PDF file for theoretical content 9 videos (3) for exercises during pregnancy Repeating relaxation (1)
Fourth session: 30-31 gestational weeks	-Risk factors during pregnancy	-Learning the signs of preterm childbirth and how to react to them	1 video clip for theoretical content 9 videos (4) for exercises during pregnancy 1 podcast for relaxation (2)
Fifth session: 32-33 gestational weeks	-Planning for delivery and selecting the type of delivery	-Natural delivery vs. cesarean section -Different pain control methods during labor -Selecting the location and necessary equipment for delivery	2 video clips and 1 PDF file for theoretical content Repeating relaxation (2) Visiting the delivery room in person
Sixth session: 34-35 gestational weeks	-An introduction to vaginal delivery	-An introduction to birth hormones -An introduction to labor stages and self-care at each stage	1 video clip, 1 PDF file, and 2 videos for theoretical content 11 videos for labor and childbirth 1 podcast for breathing techniques 1 podcast for relaxation techniques (3)
Seventh session: 36 gestational weeks	-Postpartum care and breastfeeding	-Postpartum care and recognition of dangerous symptoms -An introduction to breastfeeding methods and breast diseases -An introduction to postpartum exercises	1 video clip, 1 PDF file, and 8 pictures for theoretical content 8 videos for massage during pregnancy and labor Repeating relaxation (3)
Eighth session: 37 gestational weeks	-Neonatal care	-Neonatal care and risk factors	2 PDF files and 2 videos for theoretical content 9 videos for postpartum exercises Repeating relaxation (1)

The questions asked on the Telegram room will be answered by the researcher at least twice a day. During the last weeks of pregnancy and after uploading all files, the educational content regarding labor and childbirth preparation methods will be reviewed. To ensure the accurate learning of breathing and relaxation techniques, two 2-h long sessions will be held for the in-person training of the study group A at the hospital along with the fifth and eighth sessions of the study group B. Also, to ensure that the messages are read by the participants, before joining the group, they will be asked to share their last seen status with the researcher. Moreover, they will be required to be online at least once a day to watch the videos or read the messages sent. The last seen time of the participants will be controlled by the researcher, and those who are not online, have not seen the messages, or have not given feedback for 7 days will be contacted by message at first. If no response is received from them, the researcher will contact them through a direct phone call to ask their reasons for not responding the messages. If needed, another cell phone number will be obtained to re-send the Telegram messages to that number. Otherwise, the subject will be excluded from the study.

On the other hand, subjects in the study group B will participate in eight 2-h long sessions during the 20-37 weeks of gestation. The educational sessions will be held at the hospital based on the guidelines of the Ministry of Health. In each session, 1 h will be allocated to teaching theoretical content followed by 45 min of teaching stretching, breathing, and relaxing techniques, as well as practical strategies for posture correction and massage therapy education. The participants will be given 15 min to ask any questions, which will be answered by the researcher.

The teaching instructors for the training sessions will be midwives who are certified as childbirth educators. If needed, they will use textbooks, video and audio files, music, posters, medical moulages, whiteboard, and slides. Table 1 presents the content, time, and objectives of the educational sessions that are similar for both study groups. To increase the generalizability of the results, another group will be considered as the control group that receives no education about pregnancy and childbirth preparation. It is important to note that all three groups will receive the routine prenatal care provided at the hospital. All participants will also be followed up until delivery.

### Measurements and feasibility outcomes

The primary outcome of the present study would be the study feasibility that will be assessed based on recruitment and intervention adherence for all of the participants in both groups.

The secondary outcome of the present study would be the improvement of pregnancy experience measured by the brief version of the pregnancy experience scale (PES) [19]. The secondary outcome would be the decreased FOC measured by the version A of Wijma Delivery expectancy/experience questionnaire (WDEQ-A) [20]. In addition, the other outcomes would be the birth preference and type of delivery, respectively. Data collection is shown in the flow diagram (Fig. 1). Data will be collected at 3 times by self-reporting method through Telegram messages: Recruitment (demographic characteristics questionnaire, PES, WDEQ-A) ≈ 18-20 weeks (T1); 36-38 weeks (PES, WDEQ-A, and birth preference) (T2); the first few days of postpartum (type of delivery) (T3).

### Sample size

A useful introduction to feasibility and pilot studies is given by Sim and Lewis, who recommend at least 50 participants. Therefore, according to strong evidence, sample size 50 is considered in current study [21–23].

To determine the sample size for other variables in the present study, the sample size has been calculated with a test power of 80% and a significance level of 0.05. Moreover, it is considered that in-person and social media-based education could affect the type of delivery among the study groups, leading to a 25% decrease in cesarean sections, compared to the control group. By using the effect size equation and considering 10% sample drop, the total sample size has been estimated at 55 participants per group. It should be noted that the ratio of primiparous women undergoing a cesarean section in Iran is assumed to be 0.55 [24] based on the statistics, so the sample size is large enough to measure all variables in this study.$$n=\frac{{\left({z}_{1-\alpha\left/ 2\right.}\sqrt{2\overline{p}}\overline{q}+{z}_{1-\beta}\sqrt{p_1{q}_1+{p}_2{q}_2}\right)}^2}{{\left({p}_1-{p}_2\right)}^2}=\frac{{\left[\left(1.96\times \sqrt{2\times 0.42\times 0.57}\right)+\left(0.84\times \sqrt{\left(0.55\times 0.45\right)+\left(0.3\times 0.7\right)}\right)\right]}^2}{{\left(0.55-0.3\right)}^2}=50$$$$\overline{p}=\frac{p_1+{p}_2}{2}$$

The sample size for the other variable of the study (fear of childbirth) was determined to be 43 participants with the confidence level of 95%, the power test of 80%, and based on the Toohil et al. study standard deviation for intervention and control group was 13.1 and 9.7, respectively with *d* = 7 [25], which was less than the sample size calculated based on the type of delivery. The sample size for the other two variables (childbirth experience and birth preference) was less than the one calculated for the above variables.$$n=\frac{{\left({z}_{1-\alpha\left/2\right.}+{z}_{1-\beta}\right)}^2\times \left({s}_1^2+{s}_2^2\right)}{d^2}$$$$n=\frac{{\left(1.96+0.84\right)}^2\times \left({9.7}^2+{13.1}^2\right)}{7^2}\approx 43$$

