### Analytic plan

Feasibility of recruitment will be achieved if ≥ 30% of eligible participants enroll in the study, and ≥ 80% participants complete follow-up assessments at 36-38 weeks (PES, WDEQ-A, and birth preference) (T2); the first few days of postpartum (type of delivery) (T3). Feasibility of intervention adherence will be achieved if average proportion of intervention adherence rate is ≥ 0.8 (participating in six sessions from eight at least for both the virtual and in-person childbirth preparation training groups).

The collected data will be analyzed in the SPSS software (version 19) using descriptive statistics, such as frequency distribution tables. Also, the Chi-square test and one-way analysis of variance (ANOVA) will be used to compare the quantitative and qualitative variables in three groups, respectively. In addition, the paired *t* test will be employed for intragroup comparison. The *p* value of less than 0.05 will be considered statistically significant.

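### The cesarean sample-size formula gives about 60 per group, not the printed 50, so 55 recruited per group does not give the stated 80% power

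*Protocol article*

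**What the plan says.** The Sample size section of the protocol article first takes 50 from a general recommendation for feasibility studies. For the other variables it then states that "the sample size has been calculated with a test power of 80% and a significance level of 0.05". The effect is described as education "leading to a 25% decrease in cesarean sections, compared to the control group", and "the ratio of primiparous women undergoing a cesarean section in Iran is assumed to be 0.55". The two-proportion formula is printed with its numbers filled in: 0.55 and 0.30, multipliers 1.96 and 0.84, and mean proportions 0.42 and 0.57. Its result is printed as 50. The section continues: "By using the effect size equation and considering 10% sample drop, the total sample size has been estimated at 55 participants per group". It adds that the sample is large enough for all variables, and that fear of childbirth needs 43 and the remaining two variables fewer.

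Under Research design and sampling, the total is 165 women and "The participants will be equally allocated into two studies and one control groups". The Analytic plan compares the three groups at p < 0.05. It also makes it a feasibility criterion that at least 80% of "participants complete follow-up assessments at 36-38 weeks" and after delivery.

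**The concern.** Every input and the whole substitution are printed, so the result can be checked without any outside source, and it does not come to 50. Among the outcomes for which a calculation is reported, type of delivery needs the most women, and the 55 per group (165 in total) is presented as following from it. If 50 is too low, the 80% power and the statement that the sample suffices for all variables fail on the plan's own terms.

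The wording of the effect adds to this. A 25% decrease from 0.55 would ordinarily be read as a fall to about 0.41, but the formula uses a fall to 0.30. A reader who relies on the text would think that the trial can detect a much smaller effect than the one assumed.

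At stake is how the cesarean comparison is read. A non-significant result from a trial described as having 80% power would be taken as stronger evidence of no effect than it is. The Discussion says that lessons from the study will support a large-scale grant application, so the error could also be carried into that design.

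**Working it through.** **Inputs** (all from Sample size unless noted): control rate p1 = 0.55; education rate p2 = 0.30; two-sided 5%, z = 1.96; power 80%, z = 0.84; loss 10%; three equal groups, 165 in total (Research design and sampling); follow-up criterion at least 80% (Analytic plan).

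**1. The plan's formula with its printed numbers**

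n = [1.96 × √(2 × 0.42 × 0.57) + 0.84 × √(0.55 × 0.45 + 0.30 × 0.70)]² / (0.55 − 0.30)²

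- First term: 1.96 × √0.4788 = 1.96 × 0.6920 = 1.356
- Second term: 0.84 × √(0.2475 + 0.21) = 0.84 × 0.6764 = 0.568
- Sum squared: (1.356 + 0.568)² = 3.703
- Divided by 0.0625: **59.25, so 60 per group**

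The plan prints 50. With unrounded means (0.425 and 0.575) the first term is 1.370 and n = 60.1, strictly 61.

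**2. Could another reading give 50?**

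| Reading | n per group |
|---|---|
| Unpooled variance, two-sided | 57.5 (58) |
| Arcsine effect size, two-sided | 60.0 |
| Continuity-corrected, two-sided | 68 |
| Symbolic formula as typeset, with the mean of q outside the root | about 41 |
| One-sided 5% | about 47 to 48 |

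Only the one-sided version comes near 50, and the printed 1.96 excludes it. The fear-of-childbirth formula in the same section does reproduce: (1.96 + 0.84)² × (9.7² + 13.1²) / 7² = 7.84 × 265.7 / 49 = 42.5, so 43. The fault lies in the cesarean line alone.

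**3. Numbers to recruit.** The plan's step is 50 × 1.10 = 55. From the correct result, 60 / 0.90 = 66.7, so 67 per group and 3 × 67 = 201 in total. Starting from 61, it is 68 per group and 204 in total.

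**4. Power for 0.55 versus 0.30, two-sided 5%**

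Power = Φ{[0.25 × √n − 1.96 × √(2 × 0.425 × 0.575)] / √0.4575}

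For n = 50: (1.768 − 1.370) / 0.676 = 0.588, and Φ(0.588) = 0.722.

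| Analysed per group | Pairwise power | Three-group chi-square, 0.55/0.30/0.30 |
|---|---|---|
| 44 (80% of 55) | 66.5% | 70% |
| 50 (about 10% lost from 55) | 72% | 76% |
| 55 (no loss) | 76% | 80% |
| 60 | 80% | 84% |

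The three-group column uses the noncentral chi-square with 2 degrees of freedom. It assumes that both education groups reach 0.30. An exact binomial calculation of the pairwise test gives 74% at 50 and 76% at 55. With 50 per group, 80% pairwise power needs a fall to about 0.28, or 27 points.

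**5. The 25% wording.** In the formula, 0.55 − 0.30 = 0.25, which is 25 percentage points; relative to 0.55 it is 0.25 / 0.55 = 45%. A relative decrease of 25% would mean 0.55 × 0.75 = 0.4125. The same formula then gives about 206 per group, and power at 50 per group is about 28%.

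**The case against.** The strongest points on the other side are these.

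- **Feasibility is the primary objective.** Type of delivery comes last among the other outcomes, and the feasibility thresholds do not depend on this formula. That is true, and it limits the harm to a secondary outcome. It does not make the printed power correct.
- **The 50 also comes from the feasibility recommendation, so the formula is not the sole basis for the size.** This stands in part: that justification is separate and survives. But the section attributes the 55 to the effect-size equation plus 10%, and a rule of thumb cannot support a claim of 80% power.
- **The planned test is a three-group chi-square, which has more power.** At 0.55/0.30/0.30 it does reach 80% at 55 per group, but only with no loss at all. After the planned 10% loss it has about 76%. The plan did not size on that test.
- **An 80% follow-up criterion does not contradict a 10% expected loss.** This stands. A minimum for success may lie below the expected value, so the 44-per-group figures are a sensitivity case.
- **The intended effect is clear because 0.55 and 0.30 are printed.** This largely stands. The relative reading describes a design that the formula does not use, so the wording needs clarifying and is not a second error in the calculation.
- **Exact 80% needs 61, not 60.** Correct for the unrounded formula, but minor: power at 60 is 79.9%.

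**Conclusion.** The concern holds. The printed substitution equals 59.25, so the requirement is 60 analysed per group (61 without rounding the mean proportion), and the stated 50 is an arithmetic error. With 55 recruited and 10% lost, pairwise power for 0.55 versus 0.30 is about 72%, not 80%. It is about 76% if nobody is lost and 67% at 80% follow-up. These figures rest on the plan's own rates, a two-sided 5% level and no adjustment for multiple comparisons. The three-group chi-square figures (76% at 50, 70% at 44) also assume equal benefit in both education groups.

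The effect is worded as a 25% decrease where the calculation uses 25 percentage points. The error affects the stated power for type of delivery and the claim that the sample is adequate for all variables. The feasibility criteria and the fear-of-childbirth calculation are not affected.

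**What to change.** In the Sample size section:

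1. Correct the formula result to 60 per group, which is 67 after 10% loss.
2. If 165 women are kept, replace the 80% power for type of delivery with about 72% at 50 analysed per group, and give about 67% at 80% follow-up as a sensitivity figure. If the power is to refer to the three-group chi-square, say so and give 76% and 70%. Withdraw the statement that the sample is large enough for all variables.
3. Write the effect as a reduction of 25 percentage points, from 0.55 to 0.30 (45% relative).
4. Optionally, explain how the 10% allowance relates to the 80% follow-up criterion. This is a matter of clarity.

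Keeping 165 costs only rewording and a less favourable power statement. Keeping 80% power with 10% loss would need 67 per group, 201 in total, which is 36 more women. For a feasibility study, restating the power is the proportionate choice.

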# Comparing the effect of in-person and virtual childbirth preparation trainings on the fear of childbirth (FOC) and pregnancy experience of pregnant women: protocol for a quasi-experimental feasibility study

**DOI:** 10.1186/s40814-021-00933-w

**Published:** 2021-11-05

**Keywords:** Childbirth preparation, Fear of childbirth, Pregnancy experience, Type of delivery, Virtual education, Feasibility study

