## Abstract

**Background:**

Childbirth preparation trainings are an important component of prenatal education, and pregnant women are increasingly interested in seeking information from online sources. The aim of this study is to compare the feasibility and the effects of in-person and virtual childbirth preparation training courses on the pregnancy experience, fear of childbirth (FOC), birth preference, and type of delivery among pregnant women.

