The primary objective of study is the feasibility of recruitment and feasibility of intervention adherence of participants in both in-person and virtual education groups. The secondary objectives are the effect of childbirth preparation training courses using two in-person and virtual education methods on the pregnancy experience, FOC, birth preference, and type of delivery in pregnant women.

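### The sample-size adequacy statement is not supported for virtual versus in-person training, because both calculations compare training with control

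*Protocol article*

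**What the plan says.** The title begins "Comparing the effect of in-person and virtual childbirth preparation trainings on the fear of childbirth (FOC) and pregnancy experience of pregnant women", and the Abstract (Background) gives the aim as "to compare the feasibility and the effects of in-person and virtual childbirth preparation training courses". The Introduction ranks the objectives: "The primary objective of study is the feasibility of recruitment and feasibility of intervention adherence of participants". The effects on pregnancy experience, fear of childbirth, birth preference and type of delivery are secondary.

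The Sample size section contains two effect calculations.
- **Type of delivery.** It states that "the sample size has been calculated with a test power of 80% and a significance level of 0.05". It supposes that "in-person and social media-based education could affect the type of delivery among the study groups", with a 25% fall relative to control. The formula uses 0.55 and 0.30 and prints 50 per group, raised to 55 for 10% dropout.
- **Fear of childbirth.** It uses standard deviations of 13.1 (intervention) and 9.7 (control) with a difference of 7, and prints 43.

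The first calculation is followed by the conclusion "so the sample size is large enough to measure all variables in this study". The Analytic plan names three-group chi-square tests and one-way ANOVA, with paired t tests within groups. Its general rule is that a p "value of less than 0.05 will be considered statistically significant".

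**The concern.** The comparison in the title and aim is between two active forms of training, but the sample was sized on each form against no training. Crediting both forms with the same fall in cesarean sections implies a rate of 0.30 in each, so no virtual versus in-person difference entered the calculation. The protocol also gives no margin and no target precision for that contrast.

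A general statement that the sample is adequate invites the reader to apply it to the comparison in the title. The named tests do not correct this: a three-group p-value does not by itself say whether virtual differs from in-person, or by how much. If the two forms differ by a moderate amount, the study will probably not detect it, and the protocol does not warn that such a result would be inconclusive. The Discussion says that the lessons will be used to refine the intervention and apply for a larger grant. For that purpose an estimated difference with its interval is more useful than an overall p-value.

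**Working it through.** **Inputs from the Sample size section.** Cesarean 0.55 (control) and 0.30 (training); WDEQ-A standard deviations 13.1 and 9.7, difference 7; two-sided z = 1.96; 80% power, z = 0.84; 55 per group less 10% dropout, 55 × 0.9 = 49.5, about 50 evaluable.

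**1. The plan's own figures.**
- Fear of childbirth: (1.96 + 0.84)² × (9.7² + 13.1²) / 7² = 42.5, so 43. This reproduces.
- Cesarean, with the numbers as printed: [1.96 × √(2 × 0.42 × 0.57) + 0.84 × √(0.2475 + 0.21)]² / 0.25² = (1.356 + 0.568)² / 0.0625 = 59.3. The printed 50 does not reproduce. Power for 0.55 versus 0.30 is 72% at 50 per group and 76% at 55. This is a separate matter, but it affects how the adequacy sentence can be reworded.

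**2. Virtual versus in-person, cesarean.** Assumption: 0.30 in both training arms, as the calculation implies.
- 95% interval half-width = 1.96 × √(2 × 0.30 × 0.70 / n): 0.180 at n = 50 and 0.171 at n = 55.
- Power = Φ{[d√n − 1.96 √(2p̄q̄)] / √(p₁q₁ + p₂q₂)}, where d is the difference and p̄ the mean of the two rates. For 0.30 versus 0.40 at n = 50: (0.707 − 1.322) / 0.671 = −0.917, so 18%.

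| In-person vs virtual rate (either way round) | Power, n = 50 | Power, n = 55 |
|---|---|---|
| 0.30 vs 0.40 | 18% | 19% |
| 0.30 vs 0.45 | 34% | 37% |
| 0.30 vs 0.50 | 53% | 57% |

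- Difference detectable with 80% power: about 27 points at n = 50 (0.30 versus about 0.575) and 26 at n = 55. The effect assumed for training versus control is 0.55 − 0.30 = 25 points.

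**3. Virtual versus in-person, WDEQ-A.** Both arms are training arms, so 13.1 is the natural standard deviation. The more favorable alternative pools both printed values: √[(9.7² + 13.1²) / 2] = 11.53. The standard error at n = 50 is SD × √(2/50) = 0.2 × SD, and power is Φ(d / SE − 1.96).

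| | SD 13.1 | SD 11.53 |
|---|---|---|
| Standard error | 2.62 | 2.31 |
| 95% half-width | 5.1 | 4.5 |
| Power, 7 points | 76% | 86% |
| Power, 3.5 points | 27% | 33% |

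The protocol prints no inputs for the pregnancy experience scale or birth preference, so neither can be checked.

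**4. What a margin would require.** The protocol sets none, so this is a range under assumption. With 0.30 in both arms, one-sided 0.025 and 80% power, non-inferiority on cesarean needs per arm 330 for a 10-point margin, 147 for 15, 83 for 20 and 53 for 25 [n = (1.96 + 0.84)² × 2 × 0.21 / margin²].

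**The case against.** Four arguments carry weight.

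- **The sentence is about outcomes, not pairs of groups.** In context, the variables are type of delivery, fear of childbirth and the rest. This is fair: the authors did not expressly claim power for virtual versus in-person. But it is the only general statement of adequacy for effects, and the aim compares the two forms of training on those same outcomes, so it needs limiting.
- **Feasibility is primary.** Recruitment, follow-up and adherence have their own criteria in the Analytic plan, and it is ordinary for a three-group feasibility study not to power every contrast on secondary outcomes. This stands and lowers the severity. It does not make the adequacy statement correct.
- **Fear of childbirth, which the title names, is reasonably served.** An interval of about ±5 points is narrower than the 7-point planning effect, and power for 7 points is fair to good. The severe imprecision concerns cesarean, which the title does not name, though the aim does. This stands.
- **Pairwise contrasts and intervals may be in an analysis plan that is not shown.** This also stands, so their absence is not the point here. The point is what the protocol states about its sample size.

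A reader might infer more: that a non-significant result will be taken as equal effectiveness, or that the comparison has no power at all. The documents support neither. The protocol plans no equivalence or non-inferiority conclusion and no replacement of in-person classes, so misreading is only a risk. The WDEQ-A figures rule out the claim of no power.

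**Conclusion.** The concern holds in a limited form. The adequacy statement is unsupported for virtual versus in-person training, because neither calculation addresses that contrast. The consequence is large for cesarean, where the study can separate the two forms only if they differ by slightly more than training is assumed to differ from no training. It is moderate for WDEQ-A, where a difference as large as the planning effect would probably be seen and one half that size probably would not.

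The figures assume about 50 evaluable women per group, a cesarean rate of 0.30 in both training arms, a WDEQ-A standard deviation of 11.5 to 13.1, and independent observations without adjustment. Having all 55 women per group evaluable changes them little. Because these are secondary effects in a feasibility study, the severity is modest: the protocol should be reworded, but the design need not change.

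**What to change.** - **Sample size section.** Delete the adequacy sentence, or limit it to training versus control. If it is limited, the cesarean figure must be settled first, since the printed inputs give about 60 and not 50. As it stands, only the fear-of-childbirth calculation supports the claim.
- **Same section.** Add the expected precision for virtual versus in-person: about ±18 percentage points for cesarean and about ±5 points for WDEQ-A, with the assumptions stated.
- **Analytic plan.** Report virtual minus in-person with a 95% confidence interval for each effect outcome, alongside the three-group tests. It need not become the main comparison for every outcome; that would be a preference.
- **Interpretation.** State that a non-significant result is not evidence of equivalence, and that the interval will inform the margin and size of the larger trial.

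The cost is a more modest claim and a little more analysis. No extra women are needed.
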